### Study measures

The trial will assess effectiveness of the trainings in improving self-reported knowledge, attitudes, and clinical practice behavior using previously developed and established instruments [25–27]. Study measures will be collected at three time points: directly before the training (pre-training), directly after the training is completed (post-training), and 3-month following completion of the training.

### Knowledge measures

Consistent with the cultural awareness and knowledge dimensions of the Campinha-Bacote conceptual model [28], the knowledge measure was previously developed by the study team and collected among oncologists within the COLORS pilot study [9]. The 12-item, true/false knowledge measure (Table 2) includes general (e.g., questions pertaining sexual orientation and gender identity) and cancer-specific (e.g., questions pertaining to cancer care for LGBT) items to examine knowledge of LGBT-centric clinical and cultural competency.

**Table 2 Tab2:** Knowledge questions

Question number	Question
1	Both sexual orientation and gender identity are terms that can be used to define a person’s sexual attraction to others.
2	It is important to ask your patients about both their sexual orientation and gender identity to provide them with specific resources that meet their needs.
3	To avoid confusion when treating a transgender patient, it is best to document by their biological sex pronouns in the consult notes even if they self-identify as something different.
4	All patients have similar experiences in the clinic waiting room regardless of sexual orientation and gender identity.
5	Reading material in the clinic waiting room can shape LGBT patients’ expectations about how they will be treated in the clinic.
6	Clinicians who are not LGBT can still wear a rainbow lapel pin to signal acceptance of LGBT patients.
7	LGBT people are just as likely as straight and cisgender people to have a biological family member as their primary source of social support during their cancer care.
8	If hormone therapy is not directly contra-indicated, transgender patients should continue their hormone therapy during cancer treatment, as long as they understand the risks are unknown and that they may need additional monitoring.
9	End-of-life considerations may be more complex for LGBT people, as LGBT people may be more likely to have a partner or spouse who does not have legal custody of their children.
10	It is important to build rapport with patients to indicate you are open to discuss questions not covered by standard education materials developed for heterosexual patients.
11	Standard educational materials regarding sexual side effects for cancer treatment are always easily applicable to LGBT patients.
12	It is more important to discuss body image issues with transgender cancer survivors than with lesbian, gay, and bisexual patients.

### Attitudes measures

Consistent with the cultural awareness and desire dimensions of our conceptual model, LGBT-related attitudes will be examined via the 12-item Likert-type Modern Homonegativity Scale (MHS) [29] and the Modified Attitudes Toward LGBT Patients Scale (ATLPS-M) [30]. We have modified the MHS and ATLPS-M scales to be inclusive of both sexual and gender minorities.

### Clinical practices measures

Consistent with the cultural skills and encounters dimensions of the conceptual model, LGBT-related clinical practices will be examined via 15 items from the Gay Affirmative Practice (GAP) scale [31]. This validated, Likert-type scale examines both opinions regarding which affirming practices ought to be undertaken by clinicians, as well as a self-report of one’s own LGBT-affirming and inclusive clinical practices. We have modified the GAP scale to be inclusive of both sexual and gender minorities.

### Training interventions

The experimental arm is the COLORS training, which includes both general and oncology-specific LGBT competency content. The comparison arm is composed of several web-based modules from the National LGBT Health Education Center Training website, which includes general (not oncology-specific) LGBT competency content only. The COLORS training is of comparable length (i.e., approximately 2 h) to complete as the National LGBT Health Education Center Training.

The COLORS training is a web-based training that consists of four interactive modules. Module 1 is “LGBT Basics” and focuses on SOGI terminology, intersectionality, the importance of understanding SOGI within the context of clinical care, and communication skills around discussing SOGI with patients. Module 2 is “Inclusive Environments” and focuses on the elements of the clinic environment and the messages these elements may send to LGBT patients regarding provider awareness and acceptance of LGBT patients and their support network. These elements of the environment include intake forms, non-discrimination policies, clinic decorations and reading materials, the clinic website, and clinic restrooms. In addition to calling attention to elements of the environment, this module demonstrates how oncologists can assess their own clinic environment and demonstrated actionable steps that oncologists can take to promote inclusivity and reflect that inclusivity in the clinic environment. Module 3 is “Initiating Oncology Care with LGBT Patients” and focuses on several important care considerations during the initiation of oncology care: welcoming LGBT patients’ sources of social support, making informed treatment decisions, and considerations in end-of-life discussions. Module 4 is “Issues in Cancer Survivorship among LGBT Patients” and focuses on considerations that may arise in cancer survivorship for LGBT patients, such as discussion of supportive care, body image and sexual side effects of treatment, as well as fertility concerns. Each of the modules includes a didactic portion and an interactive portion and reflect each of Campinha-Bacote’s five dimensions of cultural competency [28]: cultural awareness, cultural knowledge, cultural skill, cultural encounters, and cultural desire. The didactic portion (cultural awareness and knowledge) provides participants with module-relevant information, and the interactive portions (cultural skill, encounters, and desire) require participants to apply what they have learned to interactive case vignettes and scenarios.

The National LGBT Health Education Center Training modules are available for free online. Among participants assigned to this training will complete four modules: (1) Providing Quality Care to Lesbian, Gay, Bisexual, and Transgender Patients, (2) Affirming LGBT People through Effective Communication, (3) Achieving Health Equity for LGBT People, and (4) Improving Health Care for Transgender People. Module 1 focuses on teaching how to provide inclusive health care for LGBT patients. Module 2 focuses on how to effectively communicate with LGBT patients, including how to use affirming and inclusive language. Module 3 focuses on how to address LGBT health disparities, including how to collect and discuss information regarding sexual orientation and gender identity. Module 4 focuses on how to provide inclusive and affirming healthcare for transgender patients. Each of the modules includes didactic portions, case examples, and quizzes that serve as knowledge checks.

### Statistical analysis

The main outcomes are changes in knowledge, attitudes, and practice behaviors regarding LGBT cancer patients from pre-training to post-training assessment, as well as from pre-training to 3-month follow-up assessment (see knowledge, attitudes, and clinical practices measures listed above). We hypothesize that participants assigned to COLORS will demonstrate statistically significantly improvements in LGBT-related knowledge, attitudes, and clinical practices than participants assigned to the comparison training. Crude means with standard deviations and medians with interquartile ranges will be calculated for each measure at pre-training, post-training, and at 3-month follow-up within each study arm. Depending on the distributions of the measures, parametric or non-parametric methods, including repeated-measures analyses, will be used to test whether the measures significantly differ pre-training, post-training, and at 3-month follow-up within and between each study arm. The Holm-Bonferroni method will be used, as necessary, to adjust for multiple comparisons.

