**Methods/design:**

Study procedures include an 8-step approach for recruitment, randomization, retention, and completion of the interventions. Oncologists of any subspecialty who are currently practicing physicians will be identified from the American Medical Association Masterfile. Approximately 5000 oncologists will be sent a FedEx envelope with an invitation letter and study timeline. Electronic consent is obtained using a secure REDCap (Research Electronic Data Capture) portal hosted at the Moffitt Cancer Center (Tampa, FL) where the oncologists will complete the eligibility questionnaire, pre-training assessments, and then will be randomized to complete the COLORS training or an online general healthcare training offered by the National LGBT Health Education Center. Effectiveness of both trainings will be assessed utilizing self-reported measures of LGBT-related knowledge, attitudes, and affirming clinical practices. The measures will be collected before and directly after training completion, as well as 3-month post-training completion. The primary outcomes are changes in knowledge, attitudes, and practice behaviors regarding LGBT cancer patients from pre-test to post-test training in the COLORS training vs. the comparison training.

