### Study registration

For step 4, after informed consent is provided, oncologists will be directed to the registration page to provide an email address and demographic information including age, race/ethnicity, sexual orientation, gender identity, sex assigned at birth, and geographic region.

For step 5, oncologists will be directed to complete the pre-training study measures (described below), which include measures of LGBT-related knowledge, attitudes, and practices. In the pre-training assessment, data on medical degree (MD, DO, other, or prefer not to answer) as well as on whether the participants have friends or family that identify as part of the LGBT community will also be collected. Upon completion of the pre-training measures, participants will receive a link for a $10 Amazon gift card via email.

For step 6, after completing the pre-training measures, participants are block randomized across US census division to either COLORS training or the general LGBT competency training. Randomization will occur within 24 h of completion of pre-training measures. The REDCap randomization algorithm will be used to generate the randomization. Following randomization, study participants will receive an email with instruction on how to access and complete their training assignment, and they will be reminded to complete the training within 2 weeks. Participants will complete their assigned training at their own pace, as each website allows participants to return to where they left off.

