### Power calculations

Power calculations are based on the primary objective of detecting statistically significant differences between the two study arms in pre- to post-training changes for the four measures listed above. The power calculations were based on the independent main effect of measure. Each measure is calculated as a single summary score and the power calculations are based on the assumption that approximately 12% of oncologists will agree to participate and be randomized (*n* = 600) and approximately 85% of those who are randomized (*n* = 255 per arm) will complete the post-training. Assuming 255 oncologists per arm will complete the training, a 2-sided alpha of 5%, and standard deviation (SD) of 1.0, power was calculated for expected ranges of mean summary scores/scales with potential deltas of the means (0.1 to 0.4) between both arms (Table 3). For all ranges of mean scores, when the detected delta of a mean is ≥ 0.3 between the 2 arms, we have substantial power to detect statistically significant differences, modest power when delta is 0.2, and low power when delta is 0.1. If the observed SD is 1.5, power drops to 0.852, 0.616, 0.324, and 0.100 for the respective deltas. However, with the expected large sample size, we estimate the SDs to be ≤ 1.0 as found in our previous work [21]. Additionally, power substantially improves across all scenarios if the delta of the means between both arms is ≥ 5 (*not shown*). Notably, the deltas used for the power calculations were based on previous studies, as the measures used in this study are not clinical measures and thus do not have clinically significant or clinically meaningful cutoff scores or thresholds.

**Table 3 Tab3:** Power calculations for the proposed scales and scores

Power for (score/scale)	Delta^a^	Mean score (control arm)	Mean score (COLORS arm)
0.994 (MHS)	0.4	12.1–12.5	12.5–12.9
0.994 (GAP)	0.4	55.1–55.5	55.5–55.9
0.922 (MHS)	0.3	12.1–12.5	12.4–12.8
0.922 (GAP)	0.3	55.1–55.5	55.4–55.8
0.615 (MHS)	0.2	12.1–12.5	12.3–12.7
0.615 (GAP)	0.2	55.1–55.5	55.7–55.7
0.203 (MHS)	0.1	12.1–12.5	12.2–12.6
0.203 (GAP)	0.1	55.1–55.5	55.2–55.6

^a^Delta of two means between both arms

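### The primary test is left to the observed distributions and no baseline adjustment is named; one baseline-adjusted mean-difference model for all four measures would be clearer and more precise

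*Protocol article*

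**What the plan says.** Protocol article, Statistical analysis: "The main outcomes are changes in knowledge, attitudes, and practice behaviors regarding LGBT cancer patients from pre-training to post-training assessment". The change up to three months is listed next to it as a further main outcome. On method, the section says: "Depending on the distributions of the measures, parametric or non-parametric methods, including repeated-measures analyses, will be used to test" for differences across the three assessments, both inside each arm and from one arm to the other. It states no criterion for choosing between the two families of test and mentions no covariate.

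Power calculations names the "primary objective of detecting statistically significant differences between the two study arms in pre- to post-training changes for the four measures listed above". Its power figures, including Table 3, are for differences in mean scores of 0.1 to 0.4, with 255 completers per arm, a two-sided alpha of 5% and an SD of 1.0.

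Study registration, step 6, says that "participants are block randomized across US census division to either COLORS training or the general LGBT competency training". The pre-training measures are completed at step 5, before randomisation. The AMA Masterfile section gives the number of census divisions as nine.

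**The concern.** A t test and a rank test on change scores do not target the same quantity. The first concerns the mean difference that the trial is powered on; the second concerns a rank-based shift. The choice is a real prospect here: knowledge is a bounded 12-item true/false score, and the MHS and GAP are Likert-type scales, so skewed or ceiling-limited distributions are likely for some measures and not for others. The four primary comparisons could then be reported on different effect measures, some of them without the mean difference that Table 3 is about.

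The second issue is precision. An unadjusted change score subtracts the whole of the pre-training score, whatever the pre/post correlation. A regression on the pre-training score lets the data set the weight, corrects chance imbalance at baseline, and is at least as precise in large samples. Power Calculations itself describes power at a difference of 0.2 as only modest, so the choice of model matters most there.

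**Working it through.** **Inputs from the document.** n = 255 per arm, two-sided alpha 0.05, SD 1.0, differences 0.1 to 0.4 (Power calculations). The pre/post correlation rho is not given; it is assumed, over 0.3 to 0.8.

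**1. Reproduce the stated power.** Using the normal approximation, power = Φ(delta / (SD × √(2/n)) − 1.96), with √(2/255) = 0.0886.
- Delta 0.2: 0.2/0.0886 = 2.258; Φ(0.298) = 0.617 (stated 0.615).
- Delta 0.3: 0.3/0.0886 = 3.387; Φ(1.427) = 0.923 (stated 0.922).
- Deltas 0.4 and 0.1 give 0.995 and 0.203 (stated 0.994 and 0.203).

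The stated figures are therefore those of an ordinary unadjusted two-sample comparison of means at SD 1.0.

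**2. Effect of baseline adjustment.** Let the pre- and post-training scores have equal variance s². The change score has variance 2s²(1−rho), and the ANCOVA residual has variance s²(1−rho²). Their ratio is (1−rho²)/(2(1−rho)) = (1+rho)/2. If 1.0 is the SD of the change, the ANCOVA SD is √((1+rho)/2). For rho 0.5 that is √0.75 = 0.866, and at delta 0.2: 0.2/(0.866 × 0.0886) = 2.608; Φ(0.648) = 0.741.

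| rho (assumed) | Variance ratio | Power, delta 0.2 (change score 0.617) | Power, delta 0.3 (change score 0.923) |
|---|---|---|---|
| 0.3 | 0.65 | 0.800 | 0.988 |
| 0.5 | 0.75 | 0.741 | 0.975 |
| 0.7 | 0.85 | 0.688 | 0.957 |
| 0.8 | 0.90 | 0.663 | 0.946 |

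The article does not say whether 1.0 is the SD of a change or of a score. If it is the SD of a score, then at delta 0.2 and rho 0.3 / 0.5 / 0.7 the change-score test has power 0.480 / 0.617 / 0.830 and ANCOVA has 0.658 / 0.741 / 0.885. ANCOVA is ahead under both readings.

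**3. Census division.** If division explains an assumed 1% to 5% of the variance, the SD becomes √(1−R²), and power at delta 0.2 moves from 0.617 to between 0.622 and 0.639. That is about 0.5 to 2 points.

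**4. Rank test when data are normal.** With effective n = 255 × 3/π, power is 0.597 at delta 0.2 and 0.912 at delta 0.3, a cost of 1 to 2 points. The case against a rank test as primary is its effect measure, not its power.

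**5. Is normality needed, and does choosing the test on the data inflate type I error?** Simulation under no difference, 255 per arm, 4,000 runs each (Monte Carlo standard error √(0.05 × 0.95/4000) = 0.003), with normal, exponential and 12-item binomial data. The t test rejected in 0.047, 0.050 and 0.050 of runs, so a test of means holds its level without normality. Choosing between t and rank test by a formal normality pretest gave 0.044 to 0.050. Taking the smaller of the two p-values gave 0.057 to 0.072.

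**The case against.** The strongest reply is that a condensed article, with the full protocol and analysis plan not shown, commonly leaves covariates to those documents. This stands for census division: silence does not show that it will be ignored, and its effect is small. It answers less on the test itself, because the article does not merely omit the method. It states one that depends on the observed distributions, with change as the outcome.

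A second reply is that repeated-measures analyses are among the permitted methods, and one with a common pre-training mean in both arms would recover much of the precision. That also stands; the gain shown is against an unadjusted change-score test only.

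A reader might go further and infer any of four stronger points. The documents do not support them.
- *The baseline score is unused.* Change scores use it; what is not named is adjustment for it as a covariate.
- *The tested contrast is open.* Power calculations fixes the between-arm difference in pre- to post-training change, and the abstract agrees ("from pre-test to post-test training in the COLORS training vs. the comparison training"). The 3-month change and the within-arm tests need their role stated, but the primary contrast is given.
- *The planned test is an arm effect averaged over pre and post, which would halve the effect.* The basis would be the sentence "The power calculations were based on the independent main effect of measure". It speaks of measure, not arm; the sentence before it gives the difference in change; and the stated power reproduces with the full delta. No such test is planned.
- *Type I error is inflated.* A distribution-based choice kept it near 0.05 in simulation. Inflation appeared only when the smaller p-value was taken, which the article does not propose.

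**Conclusion.** The point holds as an improvement in the choice of method, not as an error that invalidates the trial. The article allows the effect measure to vary between the four measures for no statistical need at this sample size, and names no adjustment for a baseline score that it already collects. Against an unadjusted change-score test with a change SD of 1.0, baseline adjustment is worth about 5 to 18 points of power at a difference of 0.2 and about 2 to 6 points at 0.3, for rho from 0.8 down to 0.3. Put as sample size, ANCOVA needs 65% to 90% of the participants for the same precision.

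These sizes rest on equal pre and post variances and on a correlation that the document does not give. They would shrink if the intended repeated-measures model already uses the pre-training score efficiently.

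**What to change.** Before the outcome data are analysed, set one primary between-arm model for all four measures at the post-training assessment. Either of these serves:
- ANCOVA of the post-training score on arm, pre-training score and census division; or
- a constrained longitudinal mixed model that also includes the 3-month score, with the pre-training mean held common to both arms, terms for visit and arm-by-visit, and census division.

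Use robust standard errors so that no distributional check is needed to select the test. Report the adjusted mean difference with its 95% CI for each measure. Keep rank tests as sensitivity analyses and label within-arm comparisons descriptive.

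The cost is wording in the analysis plan: the pre-training scores and census division are already collected, and no additional participants or visits are needed. Trial status lists the trial as closed, so the change counts as pre-specified only if it is dated before the outcome data are examined. If it comes later, the adjusted model should be reported as such.

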### Power calculations

Power calculations are based on the primary objective of detecting statistically significant differences between the two study arms in pre- to post-training changes for the four measures listed above. The power calculations were based on the independent main effect of measure. Each measure is calculated as a single summary score and the power calculations are based on the assumption that approximately 12% of oncologists will agree to participate and be randomized (*n* = 600) and approximately 85% of those who are randomized (*n* = 255 per arm) will complete the post-training. Assuming 255 oncologists per arm will complete the training, a 2-sided alpha of 5%, and standard deviation (SD) of 1.0, power was calculated for expected ranges of mean summary scores/scales with potential deltas of the means (0.1 to 0.4) between both arms (Table 3). For all ranges of mean scores, when the detected delta of a mean is ≥ 0.3 between the 2 arms, we have substantial power to detect statistically significant differences, modest power when delta is 0.2, and low power when delta is 0.1. If the observed SD is 1.5, power drops to 0.852, 0.616, 0.324, and 0.100 for the respective deltas. However, with the expected large sample size, we estimate the SDs to be ≤ 1.0 as found in our previous work [21]. Additionally, power substantially improves across all scenarios if the delta of the means between both arms is ≥ 5 (*not shown*). Notably, the deltas used for the power calculations were based on previous studies, as the measures used in this study are not clinical measures and thus do not have clinically significant or clinically meaningful cutoff scores or thresholds.

**Table 3 Tab3:** Power calculations for the proposed scales and scores

Power for (score/scale)	Delta^a^	Mean score (control arm)	Mean score (COLORS arm)
0.994 (MHS)	0.4	12.1–12.5	12.5–12.9
0.994 (GAP)	0.4	55.1–55.5	55.5–55.9
0.922 (MHS)	0.3	12.1–12.5	12.4–12.8
0.922 (GAP)	0.3	55.1–55.5	55.4–55.8
0.615 (MHS)	0.2	12.1–12.5	12.3–12.7
0.615 (GAP)	0.2	55.1–55.5	55.7–55.7
0.203 (MHS)	0.1	12.1–12.5	12.2–12.6
0.203 (GAP)	0.1	55.1–55.5	55.2–55.6

^a^Delta of two means between both arms

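### Table 3 gives power for one test at an unadjusted two-sided 5%, but the primary objective covers four measures under Holm-Bonferroni, so the stated power is too high

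*Protocol article*

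**What the plan says.** The Power calculations section bases power on between-arm differences in "pre- to post-training changes for the four measures listed above". The four are the knowledge score, the MHS, the ATLPS-M and the GAP, and none is singled out as primary. Each is treated as a single summary score and powered on its own, in these terms: "a 2-sided alpha of 5%, and standard deviation (SD) of 1.0, power was calculated for expected ranges of mean summary scores/scales". Table 3 prints results for the MHS and GAP only: 0.994, 0.922, 0.615 and 0.203 for differences of 0.4, 0.3, 0.2 and 0.1. The text calls power substantial at 0.3 and above, modest at 0.2 and low at 0.1. It also gives a sensitivity case with SD 1.5, where power at 0.4 is 0.852.

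The Statistical analysis section says: "The Holm-Bonferroni method will be used, as necessary, to adjust for multiple comparisons". It does not say which tests form the family. It also counts the change to 3 months among the main outcomes, whereas the Abstract and the power section confine the primary outcome to pre- to post-training change.

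**The concern.** A power table and a multiplicity rule in one plan should describe the same test. Here the rule, if applied across the four measures of the primary objective, compares the smallest p-value with 0.05/4 = 0.0125, while every printed power figure assumes 0.05. A reader would take 0.922 or 0.615 as the chance that a given measure is declared significant in the planned analysis, and that chance is lower.

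The wording of the Holm sentence adds to the difficulty. If the adjustment applies to the four measures, Table 3 is too favourable. If it does not, Table 3 stands for each measure, but the 5% is no longer the error rate for the objective as a whole: with four independent tests it would be 1 − 0.95⁴ = 18.5%. The printed power and a 5% family-wise error rate cannot both hold.

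**Working it through.** **Inputs, all from the Power calculations section unless noted**

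- Randomised: "approximately 12% of oncologists will agree to participate and be randomized", so 0.12 × 5000 = 600.
- Analysed: "approximately 85% of those who are randomized" complete, so 600 × 0.85 / 2 = 255 per arm.
- Alpha: two-sided 0.05, not split.
- SD: 1.0, with 1.5 as sensitivity case, taken as the SD of the quantity compared between arms.
- Differences: "potential deltas of the means (0.1 to 0.4) between both arms".
- Number of primary measures: 4.
- Correlation between measures: not given. I assume a common value of 0, 0.5 or 0.8.

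**Step 1: reproduce Table 3.** The standard error of the difference at SD 1.0 is √(2/255) = 0.0886. Power ≈ Φ(δ/SE − z), with z = 1.960 at alpha 0.05. At δ = 0.3: 0.3/0.0886 = 3.387, and Φ(3.387 − 1.960) = Φ(1.427) = 0.923. The exact noncentral t gives 0.922. For 0.4, 0.3, 0.2 and 0.1 the exact values are 0.995, 0.922, 0.616 and 0.203 (0.2035 unrounded). They agree with Table 3 to within 0.001, so the table is power for one unadjusted test.

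**Step 2: Holm's first step over four measures.** Alpha is 0.05/4 = 0.0125 and z = 2.498. At δ = 0.3: Φ(3.387 − 2.498) = Φ(0.889) = 0.813 (exact t 0.810). This is a floor: a measure that passes 0.0125 is always rejected by Holm, and one that does not may still be rejected at a later step.

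**Step 3: full Holm when all four measures share the same difference.** I simulated 100,000 draws of four correlated normal test statistics with mean δ/SE and compared the ordered p-values with 0.05/4, 0.05/3, 0.05/2 and 0.05.

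| δ (SD 1.0) | Table 3 | First step, alpha 0.0125 (exact t) | Full Holm, per measure, correlation 0 / 0.5 / 0.8 |
|---|---|---|---|
| 0.4 | 0.994 | 0.978 | 0.994 / 0.992 / 0.990 |
| 0.3 | 0.922 | 0.810 | 0.905 / 0.885 / 0.870 |
| 0.2 | 0.615 | 0.403 | 0.479 / 0.481 / 0.476 |
| 0.1 | 0.203 | 0.085 | 0.092 / 0.100 / 0.107 |

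**Step 4: the SD 1.5 case.** SE = 1.5 × 0.0886 = 0.1328. At δ = 0.4: 0.4/0.1328 = 3.011. Unadjusted, Φ(3.011 − 1.960) = 0.853 (exact t 0.852, as stated). At the first step, Φ(3.011 − 2.498) = 0.696 (exact t 0.693). At δ = 0.3 the stated 0.616 becomes 0.403.

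**The case against.** The best defence is that Table 3 contains no miscalculation and states its basis: an alpha of 5% and each measure on its own. It claims neither family-wise nor joint power. The sample size comes from an expected recruitment yield, no target power is named, and no one difference is chosen as the design value. The SD assumption also matters more at δ = 0.3: moving from SD 1.0 to 1.5 takes power from 0.922 to 0.616. All of this is true and limits the weight of the point. It does not remove the mismatch, because the document states both the table and the rule, and does not say that the table ignores the rule.

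It is also fair that 0.0125 is the Bonferroni floor. If all four measures move together, the loss at δ = 0.3 is about 2 to 5 points (0.922 to between 0.905 and 0.870), not the 11 points down to 0.810. At δ = 0.4 it is negligible.

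Three stronger readings are tempting, and the document does not support them:

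- **Eight tests.** A reader might count four measures at two time points, and quote 33.7% as the error rate for eight unadjusted tests. The primary objective is pre- to post-training only; the 3-month change enters only through the main outcomes in the Statistical analysis section. The 33.7% also assumes eight independent tests with no adjustment, which the plan does not state.
- **Joint success.** A reader might infer that all measures must succeed, and so ask for joint power. That rests on the wording of the hypothesis and the Discussion, not on a decision rule. A claim requiring every measure to succeed would in any case need no Holm penalty.
- **Adjustment chosen after seeing the data.** The qualifier in the Holm sentence leaves the scope open, but it does not say this.

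**Conclusion.** The point holds for four tests. Table 3 is single-test power, and it overstates what the plan delivers once Holm-Bonferroni is applied to the four measures of its primary objective. With 255 per arm and SD 1.0, the description of power as substantial at 0.3 or more survives, since even the floor is 0.81. The description as modest at 0.2 does not: power is 0.40 at the floor and about 0.48 if all four measures share that difference, against a stated 0.615. In the SD 1.5 case, power at 0.4 drops from 0.852 to a floor of 0.693.

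The floor depends only on the plan's own n, SD and differences. The full-Holm figures also rest on equal differences across measures and on assumed correlations. This is an inexpensive correction worth making, not a flaw that undermines the design.

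**What to change.** 1. In the Statistical analysis section, delete the qualifier *as necessary* so that the adjustment is unconditional.
2. Define the Holm family as the four between-arm contrasts in pre- to post-training change. This follows the primary objective already written in the Abstract and the power section.
3. Reconcile the 3-month main outcome with that objective by placing it, together with the within-arm tests, outside the family as supportive.
4. Restate Table 3 at alpha 0.0125 as the power guaranteed at Holm's first step. Keep the present figures only if they are labelled as unadjusted, per-measure power.

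The cost is a few sentences, one table and a less favourable statement of power. Enrolment is unaffected. As the trial is listed as closed, the correction belongs in the analysis plan and the report.
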